##### Social support

To assess the level of social support, the 12-item version of the Social Support List—Interaction (SSL-I) is used [83]. This instrument consists of three scales: everyday social support, support in problem situations and esteem support, with a higher total score reflecting more support. Although investigated in a sample of the elderly, the psychometric properties of the SSL-I-12 are satisfactory and given the general nature of the questions, the SSL-I-12 seems suitable for younger respondents [84].

#### Stress-related biomarkers

##### Hair cortisol

At baseline (T0) and post-treatment (T2), hair samples closest to the scalp are collected. Hair cortisol has shown to be a validated measure and stable retrospective marker of long-term systemic cortisol levels over weeks to several months, reflecting more chronic cortisol exposure [85]. At both assessments, a short self-composed questionnaire about the use of hair treatments or products is assessed.

##### Epigenetic and inflammatory markers

At baseline (T0) and post-treatment (T2), 3 tubes of blood (16 ml) are drawn in all consenting participants to perform future analyses on epigenetic and inflammatory markers underlying the effects of TFT. The inflammatory markers C-reactive protein (CRP), Tumor Necrosis Factor-alpha (TNF-α) and Interleukin-6 (IL-6) will be examined. The DNA that will be extracted from the blood will be used for future exploratory epigenetic research. Epigenetic changes will be analyzed using microarrays, rather than specific genes.

#### Neuroimaging assessment (fMRI sub-study)

Participants in the fMRI sub-study will undergo a one-hour fMRI measurement at pre (T0) and post-treatment (T2) in a 3T scanner at the Spinoza center for neuroimaging in Amsterdam. Scanning protocols are identical for pre and post-treatment assessments. All task stimuli are presented using the open-source software Presentation. Anatomical T1-weighted and diffusion tensor imaging (DTI) scans will be obtained to assess grey and white matter structure. To quantify functional connectivity from spontaneous neural activity, T2*-weighted echo planar images (EPIs), sensitive to blood oxygenation level-dependent (BOLD) contrast, will be obtained, covering the entire brain under rest. Task-based fMRI is adopted to identify brain regions that are functionally involved in specific task performance regarding working memory performance (using the N-back task [86]) and emotion regulation (using a situation-focused volitional reappraisal task [87]).

**Table 1 Tab1:** Overview of RESET-psychotherapy measurements per assessment

Construct	Instrument	Method	Screening	T0	T1	T2	T3
Demographics	Self-composed questionnaire	Int		X			
Depression symptom severity ^1^	IDS-SR	SR	X	X	X	X	X
Depression diagnosis	MINI-S	Int		X	X	X	X
Childhood trauma	CTQ-SF	SR	X				
Subjective stress	PSS	SR		X	X	X	X
Insomnia	ISI	SR		X	X	X	X
Functioning and disability	WHODAS-II	SR		X	X	X	X
Anxiety symptom severity	BAI	SR		X	X	X	X
Suicidality	C-SSRS	Int		*	*	*	*
Alcohol use	AUDIT	SR		X			
Drug use	Self-composed questionnaire	SR		X			
Physical activity	IPAQ	SR		X			
Smoking	Self-composed questionnaire	SR		X			
Healthcare use	Self-composed questionnaire	Int					X
Previous/current depression treatment	Self-composed questionnaire	SR		X			
Content of TAU ^2^	Self-composed questionnaire	SR				X	
Content of TFT ^2^	Self-composed questionnaire	SR				X	
PTSD/ASD diagnosis	MINI-S	Int		X			
Age and context CT exposure	MACE	SR		X			
Resilience	CD-RISC2	SR		X			
Coping style	COPE-16	SR		X			
Personality	NEO-FFI	SR		X			
Stressful life events	LTE	SR		X	X	X	X
Social support	SSL	SR		X	X	X	X
Cortisol	Hair	BM		X		X	
Questions about hair sample	Self-composed questionnaire	Int		X		X	
Epigenetic and inflammatory biomarkers	Blood	BM		X		X	
Stress-related brain activity^3^	Anatomic, resting state and task-based fMRI	BM		X		X	

*T0* baseline, *T1* after 6 weeks, *T2* post-treatment, after 12 weeks, *T3* 6 months after post-treatment, *TFT* trauma-focused therapy, *TAU* treatment as usual, *PTSD* posttraumatic stress disorder, *SR* self-report, *Int* interview, *BM* biological measure,^1^ = also assessed in week 2,4,8 and 10 (during treatment), ^2^ = completed by therapists, ^3^ = only in the fMRI sub-sample, * = only assessed if participant shows risk regarding suicidality, *IDS-SR* inventory of depressive symptomatology-self rated, *MINI-S* Mini International Neuropsychiatric Interview-Simplified, *CTQ-SF* Childhood Trauma Questionnaire – Short Form, *PSS* Perceived Stress Scale, *ISI* Insomnia Severity Scale, *WHODAS-II* WHO Disability Schedule-II, *BAI* Beck Anxiety Inventory, *C-SSRS* Columbia-Suicide Severity Rating Scale, *AUDIT* Alcohol Use Disorders Identification Test, *IPAQ* International Physical Activity Questionnaire, *MACE* Maltreatment and Abuse Chronology of Exposure questionnaire, *CD-RISC2* 2-item Connor-Davidson Resilience Scale, *NEO-FFI* NEO Five-Factor Inventory, *LTE* List of Threatening Experiences, *SSL* Social Support List, *fMRI* functional Magnetic Resonance Imaging

### Statistical analysis plan

Analyses will be conducted using an intention-to-treat (ITT) approach, including all participants originally allocated to one of the treatment conditions. To estimate the intervention effect across time, linear mixed models (LMM) will be used for both primary and secondary continuous outcomes, with outcome score at different time-points as the dependent variable and time point indicators and treatment-by-time point indicator interaction terms as independent variables. For dichotomous outcomes, generalized estimating equation (GEE) will be used in order to favor population averaged above subject specific results. The significance threshold will be set at alpha = 0.05 and treatment effects will be evaluated in terms of Cohen’s *d*. Since missing data will concern the missing data from patients dropping out of the study, analyzing all observed outcome data using LMMs and GEE is appropriate when data are missing at random [88, 89]. Per-protocol (PP) analyses will be performed in which participants in the control group will be compared to participants of the experimental group who adhered to the study protocol (i.e. followed at least 75% of the minimal amount of 6 TFT sessions). No interim analyses are planned. Stress-related factors will be examined as potential determinants of the treatment effect by studying moderation and mediation (secondary analyses). When concerning moderators, the LMMs and GEE will be augmented by incorporating the corresponding moderator and treatment-by-moderator interaction term. When concerning possible underlying mechanisms using mediation analysis, hypotheses will be tested with the analytic steps outlined by Baron and Kenny, using multiple regression analyses and Sobel’s test to evaluate if the indirect effect of the independent variable on the dependent variable via the mediating variable is significant [90]. Data from the (f)MRI sub-sample will be pre-processed and analyzed using FSL (FMRIB Software Library). To estimate the intervention effect across time, LMMs will be used with structural integrity and resting-state network functionality as dependent variables/outcome measures and time point indicators and treatment-by-time point indicator interaction terms as independent variables.

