### Eligibility criteria

Inclusion criteria are: 1) age ≥ 18 years, 2) a primary diagnosis of MDD, as a ‘stand-alone’ depression diagnosis or superimposed on a PDD (i.e. the current major depressive episode (MDE) should constitute the reason and focus of treatment), confirmed with the Mini International Neuropsychiatric Interview—Simplified (MINI-S) [53] for the fifth edition of the Diagnostic and Statistical Manual of Mental Disorders (DSM-5) [54], 3) moderate to severe MDD, as reflected by a score of  ≥ 26 on the IDS-SR [52], 4) moderate to severe CT, operationalized as scoring above the validated cut-off scores on one of the domains of the CTQ-SF (physical neglect, score ≥ 10; emotional neglect, score ≥ 15; sexual abuse, score ≥ 8; physical abuse, score ≥ 10; emotional abuse, score ≥ 13) [51], and 5) an adequate mastery of the Dutch language.

The following exclusion criteria are checked during a telephone screening, based on self-report following explicit questions: 1) a primary diagnosis of PTSD or ASD (which is also assessed during the baseline assessment, using the PTSD and ASD section of the MINI-S), 2) a lifetime diagnosis of borderline personality disorder (BPD), 3) a comorbid diagnosis of a severe mental disorder, such as bipolar disorder or a psychotic disorder, 4) current substance use dependence, and 5) previously having received TFT, specifically aimed at CT. Additional exclusion criteria for the fMRI sub-study are major internal or neurological disorders, claustrophobia, being pregnant and known contra-indications for MRI investigations, such as the presence of metal objects (e.g. pacemaker, arteriovenous clips).

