### Sample size

Based on earlier results of an add-on TFT on depressive symptoms [55, 56] we estimate to detect a medium-sized between-group effect size (i.e., Cohen’s *d* = 0.50) on the primary outcome measure (depression symptom severity at post-treatment). Based on this assumption, a power of 0.8 (80%) and a two-tailed significance level of p < 0.05, the recruitment of 63 participants per treatment group is required. Considering a conservative drop-out estimate of around 20%, *n* = 79 patients per treatment group are needed, resulting in a total sample size of *n* = 158. As described by Thirion et al. (2007), fMRI analyses require a minimum of 20 participants per group for sufficient reliability [57]. However, to increase power, we strive to recruit more participants for the fMRI sub-study, aiming at a total sample of *n* = 60 (30 participants per treatment group).

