#### Secondary outcomes

##### Remission and depression symptom severity during treatment and at follow-up

To assess the trend of depression symptom severity during treatment and at 6-month follow-up, participants are asked to complete the IDS-SR online in weeks 2, 4, 8 and 10, at T1 and at T3. MDD remission is defined as a score of  ≤ 14 on the IDS-SR [65] and confirmed with the MINI-S [53]. Because of its brevity and good psychometric properties, this interview is especially convenient for diagnosing MDD patients in everyday clinical practice.

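### Remission cannot occur at T0, so the remission GEE has no baseline severity information unless the T0 IDS-SR is added, and Cohen's d does not suit this yes/no outcome

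*Protocol article*

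**What the plan says.** Eligibility criteria (Protocol article) requires a primary MDD diagnosis confirmed with the MINI-S and, separately, "moderate to severe MDD, as reflected by a score of ≥ 26 on the IDS-SR". Recruitment and study settings places the entry IDS-SR in the online screening. Table 1 lists the IDS-SR at screening and again at T0, T1, T2 and T3, and the MINI-S depression interview at T0, T1, T2 and T3. Randomisation follows the baseline assessment and is stratified by site only.

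The outcome section on remission states: "MDD remission is defined as a score of ≤ 14 on the IDS-SR [65] and confirmed with the MINI-S".

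On analysis, the Statistical analysis plan section gives the linear mixed model time indicators and treatment-by-time interactions. For binary outcomes it says: "For dichotomous outcomes, generalized estimating equation (GEE) will be used in order to favor population averaged above subject specific results". The GEE's own terms are not listed; extra terms for the LMM and the GEE are mentioned only as moderators. The sentence after the GEE sentence adds that "treatment effects will be evaluated in terms of Cohen’s" d, with no restriction to continuous outcomes.

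**The concern.** A continuous outcome can use baseline severity because the T0 score can enter the mixed model as one of the repeated measures. Remission has no such route. Its T0 value is the same for every patient in both arms, so baseline severity reaches the remission model only as a covariate, and none is named.

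Severity at entry plausibly matters for this endpoint because the threshold is absolute. A patient starting at 26 must fall 26 − 14 = 12 points to reach it; one starting at 50 must fall 50 − 14 = 36. Stratifying by site alone does not balance severity by design.

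The effect measure is a second, smaller matter. Cohen's d is a standardised mean difference. It does not describe a difference in remission proportions, and it sits awkwardly beside the stated preference for a population-averaged result. At stake are some power and the readability of the remission result.

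**Working it through.** **The plan's own sample size.** Sample size specifies "a power of 0.8 (80%) and a two-tailed significance level of p < 0.05" and d = 0.50, and concludes that "the recruitment of 63 participants per treatment group is required".

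- n per arm = 2(1.96 + 0.8416)² / 0.5² = 2 × 7.849 / 0.25 = 62.8, rounded up to 63 (normal approximation; a t-test version gives 63.8, rounded up to 64).
- With 20% dropout: 63 / 0.8 = 78.75, rounded up to 79 per arm, 158 in total.

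The stated figures reproduce. They concern the primary outcome; no power is stated for remission.

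**Remission at T0.** The MINI-S must show a current MDD at entry, and Table 1 schedules that interview at T0. Remission must be confirmed with the same interview. The two exclude each other, so T0 remission is zero in both arms. The IDS-SR alone would not prove this, because the entry score of at least 26 is a screening score. A T0 score of 14 or less would still be very rare: assuming mean 38, SD 10 and a screening-to-T0 correlation of 0.7, 0.8 or 0.9, its simulated probability is 0.16%, 0.06% or 0.003%.

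**What a T0 row does.** One simulated complete data set, 63 per arm, was fitted by logit GEE with and without the all-zero T0 rows. With them, the T0 intercept ran off to −26.6 (independence) or −29.6 (exchangeable). The T1, T2 and T3 treatment coefficients were 2.578, 0.681 and 0.074 (SE 0.769, 0.373, 0.386) in every fit. The T0 rows neither helped nor harmed.

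**Unadjusted power.** Assume TAU remission p₀ and shift the latent severity scale by d = 0.5, so p₁ = Φ(Φ⁻¹(p₀) + 0.5).

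- p₀ = 0.25: p₁ = Φ(−0.674 + 0.5) = 0.431. Pooled SE = √(2 × 0.3405 × 0.6595 / 63) = 0.0844; unpooled SE = √((0.1875 + 0.2452) / 63) = 0.0829. Power = Φ((0.181 − 1.96 × 0.0844) / 0.0829), about 57%.
- p₀ = 0.15: p₁ = Φ(−1.036 + 0.5) = 0.296, and power is about 50%.

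**Gain from the T0 score.** Two simulations used T2 logistic models with 63 evaluable per arm. A ran 4,000 trials per setting on the latent scale, adjusting and then standardising over baseline. B ran 3,000 trials with baseline IDS-SR about normal(40, 10) cut at 26, T2 SD 13, and a TAU mean at T2 of 26 (remission about 18% v 34%) or 30 (about 11% v 23%). Power, unadjusted → adjusted, in %:

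| Setting | r = 0.3 | r = 0.5 | r = 0.6 |
|---|---|---|---|
| A, 25% v 43% | 57.8 → 59.8 | 57.4 → 64.8 | 57.8 → 68.7 |
| A, 15% v 30% | 51.1 → 52.4 | 50.1 → 56.6 | 49.2 → 58.5 |
| B, 18% v 34% | 53.9 → 55.4 | 54.1 → 58.9 | 53.1 → 63.1 |
| B, 11% v 23% | 45.5 → 45.9 | 46.1 → 49.9 | 44.6 → 51.9 |

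The gains are 0.4–2.0, 3.8–7.4 and 7.3–10.9 points. At r = 0 (run in A only) there is no gain. Under no effect the rejection rate in A was 4.5–5.2%.

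**Effect on the estimand.** In A at 25% and r = 0.5, the unadjusted OR is 2.30. Adding the covariate alone gives 2.71 (2.99 at r = 0.6), because the OR is then conditional on baseline. Standardising over the baseline distribution returns it to 2.30 (2.31 at r = 0.6). The SD of the log OR falls from 0.393 unadjusted to 0.363 standardised at r = 0.5, a variance ratio of (0.363 / 0.393)² = 0.85.

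**The case against.** The strongest reply is that nothing here invalidates the planned analysis. Under randomisation an unadjusted GEE compares remission without bias and directly gives the population-averaged effect that the article wants. That stands.

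Several stronger readings are tempting, and the document does not support them:

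- **The GEE breaks down at T0.** The article does not say that T0 enters the remission model, and in the fitted example only the T0 intercept diverged.
- **The plan ignores baseline severity.** The GEE's terms are not listed, and a separate analysis plan may add covariates. What can be said is that no baseline term is named and that the only additions mentioned are moderators.
- **The entry IDS-SR by itself rules out remission at T0.** That score is taken at screening; the exclusion rests on the MINI-S diagnosis.
- **Chance imbalance in severity biases the result.** Its contribution is already in the standard error and the type I error; the issue is precision.
- **Remission is the leading secondary outcome.** It heads the list of other clinical outcomes in the second secondary objective; the first objective concerns depressive symptoms during treatment and at follow-up.

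It is also fair that adjustment is not entirely free, since the plain adjusted OR leaves the population-averaged target. The simulations also treat remission as a threshold on severity and omit the MINI-S confirmation.

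The Cohen's d sentence can be read charitably as meant for the continuous scales. As written it carries no such limit and directly follows the sentence on binary outcomes.

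**Conclusion.** The point holds as a modest efficiency and effect-measure improvement for one secondary outcome, not as a flaw in the trial's validity. Two parts follow from the text alone: T0 remission status carries no information, and Cohen's d is stated without restriction although it does not suit remission.

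The size of the power gain is conditional. It rests on d = 0.5, 63 evaluable patients per arm, assumed TAU remission of about 11–25%, and an assumed T0–T2 correlation. It is negligible at r = 0.3, worthwhile at 0.5–0.6 and absent at zero. The article gives no remission rate, IDS-SR SD or correlation with which to narrow that range.

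**What to change.** In the analysis plan, before any unblinded analysis:

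1. Fit the remission GEE to the post-baseline visits T1, T2 and T3 only, with the T0 IDS-SR total as a continuous covariate.
2. From that model, report marginally standardised remission proportions by arm at T2 and T3, with the risk difference (or marginal OR) and its 95% CI.
3. Limit Cohen's d to the continuous scales.

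No new data or patients are needed, because Table 1 already schedules the T0 IDS-SR. The cost is one covariate, one clarified sentence and one post-estimation step. That step is not optional: without it the adjusted OR is conditional on baseline and departs from the article's population-averaged aim. Settling this in advance also avoids a covariate or effect measure that appears to have been chosen from the results.

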The overall aim and primary objective of the RESET-psychotherapy (REStoring mood after Early life Trauma) study is to investigate whether TFT as an adjunctive to treatment as usual (TAU) (experimental condition) leads to more reduction of depressive symptoms at post-treatment when compared to TAU only (control condition) in MDD patients with CT. Secondary objectives are: 1) to determine whether patients who receive adjunctive TFT show more depressive symptom reduction during treatment and at 6-month follow-up than patients who only receive TAU, 2) to examine whether patients in the experimental condition show more improvement in other clinical outcomes in comparison to patients in the control condition (i.e. MDD remission rate, anxiety symptom severity, insomnia, subjective stress and overall functioning and disability), 3) to examine potential mediators (e.g. social support and stressful life events) and moderators (e.g. comorbid PTSD / acute stress disorder (ASD), timing/duration/context of CT, resilience, personality and coping) of the hypothesized beneficial effect of TFT, and 4) to understand neurobiological mechanisms of the expected clinical improvement following TFT.

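### The plan justifies GEE for remission by data missing at random, but ordinary unweighted GEE is not protected when dropout depends on earlier IDS-SR scores

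*Protocol article*

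**What the plan says.** The Statistical analysis plan section uses LMMs for continuous outcomes. For binary ones it states: "For dichotomous outcomes, generalized estimating equation (GEE) will be used in order to favor population averaged above subject specific results". It then gives one missing-data justification for both methods. It begins "Since missing data will concern the missing data from patients dropping out of the study" and concludes that "analyzing all observed outcome data using LMMs and GEE is appropriate when data are missing at random". The section names no weighting and no imputation for the GEE.

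The dichotomous outcome named in the article is MDD remission. It opens the list in the second secondary objective (Background): "MDD remission rate, anxiety symptom severity, insomnia, subjective stress and overall functioning and disability". The section on remission and depression severity requires an IDS-SR score of 14 or less, with confirmation by the MINI-S interview. On dropout, the Sample size section says "Considering a conservative drop-out estimate of around 20" (per cent).

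**The concern.** Missing at random allows dropout to depend on anything already observed, including earlier depression scores. A likelihood-based LMM uses those scores and so allows for such dropout. Unweighted GEE solves estimating equations on the observed outcomes and does not rest on a full likelihood. In general it is consistent only if missingness is completely at random or depends only on covariates in the mean model. The plan therefore defends both methods by an assumption that protects only one of them.

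At stake are the remission rates per arm and, if dropout works differently in the two arms, the odds ratio between them. Such a difference is possible here: patients and therapists know the allocation, and one arm receives 6 to 10 additional trauma-focused sessions. A later analysis plan that followed the sentence would carry the error forward.

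**Working it through.** **1. The plan's own figures.** With d = 0.50, two-sided alpha 0.05 and power 0.80, n = 2 × (1.960 + 0.842)² / 0.50² = 62.8, so 63 per arm. Then 63 / (1 − 0.20) = 78.75, so 79 per arm and 158 in total. The stated sample size reproduces. The article gives no figure for remission.

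**2. Why the GEE estimate moves.** Take an independence working correlation and a separate mean for each arm and visit. The GEE estimate of remission at T2 is then the proportion of remitters among patients still present. If π is the probability of being observed given the week-6 (T1) score, that proportion estimates E[π × remission] / E[π]. It equals the true rate only if π is unrelated to T2 remission within the arm. Weighting each observed patient by 1/π restores the true rate.

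**3. First illustration.** All inputs are assumptions, since the article gives no trajectories:
- IDS-SR means at T0, T1 and T2 of 40, 34, 30 (TAU) and 40, 31, 24 (trauma-focused therapy, TFT).
- SDs 9, 11, 12; correlations 0.6 (T0–T1), 0.5 (T0–T2), 0.75 (T1–T2).
- Remission taken as IDS-SR ≤ 14, without the MINI-S.
- Dropout of 20% after T1. Where it is informative, its odds are multiplied by e per SD of the T1 score.

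True rates: TAU Φ((14 − 30)/12) = 9.1%; TFT Φ((14 − 24)/12) = 20.2%. The odds ratio is (0.202/0.798) / (0.091/0.909) = 2.53 (2.54 in the simulated data).

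Results with one million patients per arm, unweighted GEE with independence:

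| Dropout | TAU | TFT | Odds ratio |
|---|---|---|---|
| Truth | 9.1% | 20.2% | 2.53 |
| Higher scorers leave both arms | 10.7% | 23.3% | 2.54 |
| Informative in TAU only | 10.7% | 20.2% | 2.11 |
| Informative in TFT only | 9.1% | 23.3% | 3.03 |

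With the same mechanism in both arms, the rates are too high by 1.6 and 3.1 points. The odds ratio is unchanged, while the risk difference goes from 11.1 to 12.6 points. Inverse-probability weighting gave odds ratios of 2.53 to 2.55 throughout.

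**4. Second illustration.** This used different assumed trajectories over T0 to T3, with dropout depending on the last observed score.
- Completely random dropout: no material bias.
- Higher scorers leave both arms (21% missing at T2): 18.2% and 34.6% against true rates of 15.5% and 30.9%; odds ratio 2.38 against 2.43. Weighting gave 2.43.
- An exchangeable working correlation gave 17.6% and 33.9%. It reduced the bias without removing it.

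**5. Size against sampling error.** With 63 observed patients per arm at 20% and 9%, the standard error of the log odds ratio is √(1/12.6 + 1/50.4 + 1/5.67 + 1/57.33) = 0.54. The shift with informative dropout in TAU only is ln(2.11/2.53) = −0.18, about a third of one standard error.

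**The case against.** The strongest reply is that little in the trial depends on this. The primary outcome is the continuous IDS-SR at T2, analysed by an LMM, for which the sentence is correct. The continuous secondary outcomes are also untouched. The article calls the 20% conservative, and the data management section encourages patients who stop treatment to continue assessments. If dropout works alike in both arms, the odds ratio barely moves. All of this stands and limits the weight of the point. It does not make the sentence right: fewer missing values do not make GEE valid under missing at random. Nor is this a detail left to a separate analysis plan, because the objection is to a statement that the article makes.

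A reader might infer more, and the documents do not support it:
- **That GEE strictly needs data missing completely at random.** Missingness that depends only on modelled covariates, here arm and time, is also tolerated.
- **That the odds ratio will be far off.** Under the first illustration it can reach 1.6 or 4.4, but only if sicker patients leave one arm while healthier patients leave the other, each with a strong dependence on the score. Nothing in the article suggests this. Halving the slope in the TAU-only case gives 2.25.
- **That a baseline term in the GEE cannot be estimated because nobody is in remission at T0.** The article does not write out the GEE terms, so this cannot be held against it.
- **That dichotomising wrongly discards the scores from weeks 2 to 10.** Those scores are collected for the severity trend. Table 1 schedules the MINI-S only at T0 to T3, so those weeks could not be remission time points. Using the scores to handle dropout would be an improvement and does not correct an error.

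**Conclusion.** The statement is wrong as written and should be fixed. Missing at random supports the LMMs but not ordinary unweighted GEE. The consequence is confined to dichotomous outcomes, in practice remission. If dropout depends on earlier IDS-SR scores, the remission rates are biased, by about 2 to 3 points in the first illustration and up to about 4 in the second. The odds ratio is biased when the mechanism differs by arm, for example 2.5 becoming 2.1, and is essentially unchanged when the mechanism is the same. These sizes rest on assumed trajectories, correlations and dropout models; the error in the statement does not. The primary analysis and the sample size are unaffected.

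**What to change.** Reword the sentence so that validity under missing at random is claimed for the LMMs only. For remission, prespecify one of two approaches:
- **Inverse-probability-weighted GEE**, with weights from a dropout model containing arm and earlier observed IDS-SR scores.
- **Multiple imputation** of missing IDS-SR and MINI-S values using arm and the repeated IDS-SR scores, followed by GEE on the imputed data.

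Both keep the population-averaged effect that the plan asks for. T0 IDS-SR should not be added to the GEE as a covariate unless risks are standardised back to the marginal scale. The odds ratio is non-collapsible: with complete data in the first illustration, that adjustment alone moves it from 2.54 to 2.88.

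The cost is some wording and modest extra analysis, with no new data. The weighting or imputation model must be parsimonious because remitters may be few: at the assumed 9.1%, about 7 of the 79 patients in TAU.

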#### Treatment as usual (TAU)

TAU for MDD is determined by the Dutch multidisciplinary practice guideline for depression [59]. This means that patients with MDD and CT receive good clinical care, e.g. evidence-based pharmacotherapy (antidepressant medication), combined with/or evidence-based psychotherapeutic interventions, such as CBT or interpersonal therapy (IPT). To determine the content of treatment, detailed information about the type of TAU, the number of sessions, treatment duration, treatment setting and treatment form is assessed by using a self-composed questionnaire that therapists need to complete after the post-treatment assessment (T2 at 12 weeks, see Table 1). Up to T2, TAU therapists are instructed to not provide TFT for CT to minimize treatment contamination [60]. To somewhat even the number of contact moments between the two conditions, patients in the control condition are offered extra contact moments with a RA when they complete the IDS questionnaire from home in week 2,4,8 and 10 (Table 1). In addition, patients in the control condition are encouraged to participate in monthly online group sessions in which a specific theme relevant to mental health (i.e. sleep, activity, stress) is discussed by an expert in this field. Because of these extra contact moments, the treatment for patients in the control group could be described as an enriched TAU.

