### Data management and quality assurance

After inclusion, participants receive a unique, coded participant number that contains no identifiable information. All data are collected digitally whenever possible, using Castor EDC, and de-identified using this coded number. An administrative database will be used to ensure timely assessments. Participants who discontinue their treatment or deviate from the study protocol are encouraged to continue the research assessments to minimize loss of follow-up data. Once collected, de-identified data are backed up periodically and centrally stored and managed by the data management team of the Amsterdam UMC. Data will be stored 15 years upon completion of the study and will be destroyed after this time. The video recordings and/or audio recordings of the TFT sessions are securely stored at the digital network of the mental health organization where the participant receives treatment. The recordings will be destroyed one year upon completion of the study. The study is guided by the study team, which also acts as the steering committee. The study team consists of the PI, co-principal investigators, junior researchers, RA’s, and site investigators (Additional file 1: Appendix C). All amendments to the study protocol will be notified to the accredited MREC. A meta-analysis shows that a small percentage of patients deteriorate from psychotherapy [91]. However, previous studies on (additional) trauma treatments for depression reported no adverse side effects of treatment [48, 56, 92]. In our study, the well-being of study participants and study procedures will be properly monitored. Accordingly, an independent clinical research associate (CRA) of the Clinical Monitoring Center (CMC) of the Amsterdam UMC carries out monitoring visits during and after the study based on a study-specific monitoring plan. Therefore, extra monitoring is not considered necessary and a data monitoring committee (DMC) is not installed.

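### The per-protocol analysis drops non-adherers from the TFT arm only, so its estimate is not protected by randomisation and can be biased in either direction

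*Protocol article*

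**What the plan says.** The Statistical analysis plan section of the protocol article makes intention-to-treat the general approach: "Analyses will be conducted using an intention-to-treat (ITT) approach, including all participants originally allocated to one of the treatment conditions". It then adds per-protocol analyses in which "participants in the control group will be compared to participants of the experimental group who adhered to the study protocol". An adherent patient is one who "followed at least 75% of the minimal amount of 6 TFT sessions". No matching rule is set for controls. The models named there contain "time point indicators and treatment-by-time point indicator interaction terms as independent variables", and no predictor of adherence is listed. The section does not say what role the per-protocol result will play.

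Two other places bear on the point. Under Data management and quality assurance, "Participants who discontinue their treatment or deviate from the study protocol are encouraged to continue the research assessments", so outcomes of non-adherers should largely be available. Under Treatment as usual (TAU), "Up to T2, TAU therapists are instructed to not provide TFT for CT to minimize treatment contamination".

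**The concern.** Session attendance is known only after randomisation and can be observed only in the TFT arm. Removing patients who attended fewer than 5 sessions leaves a selected experimental group. The controls remain a mixture of those who would have attended and those who would not. If attendance is related to how a patient would have fared anyway, the contrast mixes any TFT effect with that difference in prognosis.

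A per-protocol estimate is readily taken as the effect of TFT in those who actually had it. If it were larger than the intention-to-treat estimate, this definition gives no means of telling a real effect among attenders from selection.

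**Working it through.** **The plan's own figure.** Sample size section: d = 0.50, power 80%, two-sided 5%.
n per arm = 2 × (1.960 + 0.842)² / 0.50² = 62.8, so 63. With 20% drop-out, 63 / 0.80 = 78.75, so 79 per arm and 158 in total. This agrees with the article.

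**Adherence cut-off.** 0.75 × 6 = 4.5, so at least 75% means 5 or more sessions.

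**Bias when TFT has no effect.** Let q be the share who would not adhere and g the outcome gap in SD units, would-be non-adherers minus adherers. A higher IDS-SR score is worse. By randomisation q and g are the same in both arms.
- Control mean = (1 − q) × m(adherers) + q × m(non-adherers)
- Per-protocol TFT mean = m(adherers)
- Control minus TFT = q × g

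The documents state neither q nor g. The 20% in the Sample size section is study drop-out, not session non-adherence. The values below are assumptions. Type I error comes from simulation with 79 per arm, complete data, a comparison of means at T2, and 40,000 runs per row.

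| q | g (SD) | Bias (SD) | Per-protocol type I error |
|---|---|---|---|
| 0.10 | 0.5 | 0.05 towards TFT | 6.0% |
| 0.20 | 0 | 0 | 4.9% |
| 0.20 | 0.5 | 0.10 towards TFT | 9.2% |
| 0.20 | −0.5 | 0.10 towards control | 9.1% |
| 0.20 | 1.0 | 0.20 towards TFT | 23.4% |
| 0.30 | 0.5 | 0.15 towards TFT | 14.0% |
| 0.40 | 0.5 | 0.20 towards TFT | 19.7% |

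In the same runs the intention-to-treat comparison stayed between about 4.8% and 5.2%.

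**Check by hand for q = 0.20, g = 0.5.** The variance among adherers is 1 − 0.8 × 0.2 × 0.5² = 0.96. The standard error is √(1/79 + 0.96/(0.8 × 79)) = 0.167. Bias / SE = 0.10 / 0.167 = 0.60. The chance of |z| > 1.96 is Φ(−1.36) + Φ(−2.56) = 0.087 + 0.005 = 9.2%, as simulated.

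**Relative size.** 0.10 / 0.50 = one fifth of the planned effect.

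**The case against.** The strongest reply is that this analysis is secondary. Intention-to-treat on everyone randomised comes first, and follow-up of those who stop treatment supports it. That stands: the primary conclusion is not at risk. The role of a supplementary analysis may also be set out in a fuller document that is not shown. That stands too, but the definition itself is in the article, and it is the definition that fails.

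Several stronger readings are tempting and are not supported.
- A reader might infer that the analysis will show a TFT benefit where none exists. That needs non-attenders to have a worse prognosis. With no gap there is no bias, and if early improvers stop, the same bias runs against TFT. The article gives no data on either.
- A reader might object that 4.5 sessions cannot be attended. The wording of a minimum plainly means 5 or more, so this is no defect.
- A reader might infer that the 6-month contrast is biased, because the objectives describe benefit "at 6-month follow-up than patients who only receive TAU" while the instruction against TFT for controls runs only up to T2. Intention-to-treat at T3 remains a valid comparison of assigned strategies, and the phrase can be read as an arm label. Later TFT in controls changes what the contrast estimates and may dilute it.
- TFT reaching controls before T2 is possible but barred by instruction. It would ordinarily shrink the contrast.

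It can also be said that a complier analysis has weaknesses of its own. This stands and shapes the fix. Using the 5-session threshold as the exposure assumes that 1 to 4 sessions do nothing. Assignment also acts through other routes: controls alone are offered extra contacts with a research assistant and encouraged to join group sessions, and patients know their arm while the primary outcome is self-reported.

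**Conclusion.** The concern holds in limited form. As written, the per-protocol contrast selects on a post-randomisation variable in one arm, with no named adjustment, and its estimate is not protected by randomisation. The direction of bias cannot be settled from the article. For non-adherence of 10% to 40% and a gap of 0.5 SD either way, the bias is 0.05 to 0.20 SD in size. The middle case of 20% gives 0.10 SD and a type I error of about 9%. These figures rest on assumed adherence and prognosis, complete data, and a simple comparison at T2. The gap means the part of prognosis that the fitted model leaves unexplained. The intention-to-treat result is untouched, so this is a change that should be made to a supporting analysis and not a threat to the trial's main conclusion.

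**What to change.** Replace the per-protocol contrast, or label it supportive, and specify a complier average causal effect at T2:
- Use randomised assignment as the instrument, adjusting for baseline IDS-SR and site. Without covariates the estimate is the intention-to-treat difference divided by the between-arm difference in the proportion receiving TFT. Its numerator has expectation zero if assignment has no effect.
- Make receipt of any TFT the main exposure, with 5 or more sessions as a sensitivity analysis. Count TFT given to controls as non-compliance.
- State the exclusion restriction and its limits: possible effects of sub-threshold sessions (for the threshold version), the extra contacts in the control arm, and unblinded self-report.
- For T3, at most add a sentence saying that the comparison is of assigned strategies, because the instruction to withhold TFT from controls runs only up to T2.

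The change is to analysis wording. Therapist questionnaires on TAU and TFT content at T2 and no-shows from health records are already planned. The sponsor should confirm that they capture TFT session counts and any TFT given to controls.

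The price is precision and an untestable assumption. If 80% of the TFT arm and no controls met the exposure definition, with 79 per arm, the standard error would be √(2/79) / 0.80 = 0.199 SD, against 0.167 SD for the per-protocol contrast. That is an interval about 19% wider.
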